## Abstract

**Background:**

Findings from both epidemiological and basic research point to the possibility that NSAIDS impede the deterioration in schizophrenia.

**Methods:**

To study the efficacy of acetylsalicylic acid we will perform a randomized placebo controlled double-blind add-on trial of 80 inpatients and outpatients with schizophrenia, schizophreniform or schizoaffective disorder. Patients will be 1:1 randomized to either 3 months 1000 mg acetylsalicylic acid per day or 3 months placebo, in addition to their regular antipsychotic treatment. All patients will receive pantoprazole treatment for gastroprotection. The outcomes of this study are 3-month change in psychotic and negative symptom severity, cognitive function, and several immunological parameters.

This trial may (1) yield a new (adjuvant) therapy for schizophrenia and (2) add to the knowledge on the pathogenesis of this major psychiatric disorder.

## Background

Despite several advances in the treatment of schizophrenia, currently available pharmacotherapy does not change the course of illness or prevent functional deterioration in a substantial number of patients. Therefore, research efforts into alternative or adjuvant treatment options are needed. In this project we will empirically investigate the effect of the anti-inflammatory drug acetylsalicylic acid as an add-on to regular antipsychotic therapy on the symptoms of schizophrenia.

There are several observations and theoretical considerations that support the hypothesis that anti-inflammatory drugs can be effective in antagonizing the process underlying the clinical deterioration in schizophrenia. In numerous epidemiological and clinical studies an inverse relationship between schizophrenia and rheumatoid arthritis has been demonstrated, i.e. these conditions rarely coexist in one person [1,2]. A possible explanation for this relationship implies that the use of anti-inflammatory drugs by patients with rheumatoid arthritis protects them against the development or progression of schizophrenia. This hypothesis is supported by the observation, made in a recent population-based study, that not only rheumatoid arthritis is far less frequent among patients with schizophrenia, but also other musculoskeletal conditions commonly treated with anti-inflammatory drugs[3]. These conditions were osteoarthritis of the knee, hip and spine, low back pain, and intervertebral disc disorders.

The hypothesis of the effectiveness of anti-inflammatory drugs in schizophrenia is also supported by more basic science findings. A prominent hypothesis concerning the pathogenesis of schizophrenia implicates dysfunction of the N-methyl-D-aspartate acid (NMDA) receptor [4]. This hypothesis suggests that in schizophrenia progressive excitotoxic neuronal cell death occurs via disinhibition of glutamatergic projections to hippocampal and cortical areas [5]. In this respect, prostaglandins may play an important role in two ways: (1) because they are intermediaries in the postsynaptic signal transduction cascade of cells with NMDA-type glutamate receptors and (2) by potentiating glutamatergic transmission by inhibiting astrocytic reuptake of glutamate. Both mechanisms can potentiate excitotoxic cell death[6]. As non-steroidal anti-inflammatory drugs (NSAIDs) inhibit prostaglandin synthesis through the inactivation of cyclooxygenase, they may be of therapeutic value in schizophrenia. This mechanism may also play a role in the recently confirmed inverse relation between long-term use of NSAIDs and the risk of Alzheimer's disease[7]. The therapeutic potential of acetylsalicylic acid is further suggested by the results of an experiment performed by Grilli et al., who reported that acetylsalicylic acid and its metabolite sodium salicylate protected against neurotoxicity elicited by the excitatory amino acid glutamate in rat neuronal cultures and hippocampal slices[8].

Alternatively, NSAIDS may ameliorate symptoms of schizophrenia by affecting neuronal membrane phospholipids. As suggested by Horrobin a decreased incorporation of arachidonic acid and docosahexaenoic acid into membrane phospholipids combined with an increased removal of these essential fatty acids hamper normal neurodevelopment and adult neuronal functioning [14]. Each of these abnormalities may be related to an altered activity of phospholipase A_2_. As acetylsalicylic acid inhibits phospholipase A_2 _this NSAID may yield clinical improvement in schizophrenia[1].

Finally, a recent study showed cyclo-oxygenase hyperactivity in platelets of schizophrenic patients[15]. If also present in the brain this further implicates acetylsalicylic acid as a potential therapeutic agent for schizophrenia.

As cyclooxygenase-1 and cyclooxygenase-2 are both constitutively expressed in the brain [16], both the older COX-1 NSAIDS such as acetylsalicylic acid and indomethacin and the newer selective COX-2 NSAIDS such as celecoxib may theoretically impede the pathologic process in schizophrenia. We are aware of only one clinical trial that examined the potential therapeutic role of NSAIDS in schizophrenia. It demonstrated a beneficial effect of the COX-2 inhibitor celecoxib as an add-on therapy during five weeks on schizophrenia psychopathology in 50 patients[17]. We decided to study the efficacy of the non-selective classical NSAID acetylsalicylic acid because of its neuroprotective effect in rat neuronal cultures and, in view of the epidemiological inverse relation between schizophrenia and rheumatoid arthritis, because of its past widespread use in the treatment of rheumatoid arthritis.

### Research questions

Does 1000 milligrams of acetylsalicylic acid daily reduce symptoms of schizophrenia? Is this effect modified by initial relative TH-2 reactivity?

### Study objectives

To determine the effect of three months additional treatment with acetylsalicylic acid on positive, negative and cognitive symptoms as well as immunological parameters in patients treated with antipsychotics for schizophrenia. A secondary objective is to examine whether this effect is modified by initial relative TH-2 reactivity.

## Design and methods

### General

We will perform a randomized, placebo-controlled, double-blind multicenter trial of 80 inpatients and outpatients with schizophrenia, schizophreniform or schizoaffective disorder.

### Inclusion criteria

To be included in the study one has to give written informed consent, be diagnosed with schizophrenia, schizophreniform or schizoaffective disorder according to DSM-IV, aged between 18 and 55 years old, with disease duration less than 10 years. All participants have to be clinically stable, meaning no change in dose of antipsychotic drugs 2 weeks before inclusion. At randomisation all participants need to have a score of at least 60 on the total score of the Positive and Negative Syndrome Scale (PANSS) with two scores of at least 4. For safety reasons participants are not allowed to have a contraindication for, or be hypersensitive to acetylsalicylic acid or pantoprazole, have a significant somatic illness or be pregnant. Participants are not allowed to use corticosteroids or chronically use of nonsteroidal anti-inflammatory drugs (NSAIDs) or platelet inhibitors. Persons with drugs dependencies are not allowed to participate.

### Screening

Patients will be recruited at the Department of Psychiatry of the University Medical Center Utrecht, 'Symfora Amersfoort', 'Psychiatric Center AMC/de Meren, Amsterdam', 'Spatie Apeldoorn', 'Stichting de Geestgronden', 'Adhesie Deventer', 'RIAGG Amersfoort' and the 'Delta pychiatric hospital'. If the treating responsible psychiatrist considers a patient eligible for study, his diagnosis will be confirmed according to the Diagnostic and Statistical Manual of Mental Disorders fourth edition (DSM-IV) using the Comprehensive Assessment of Symptoms and History (CASH). The PANSS will be filled out and the remaining inclusion criteria will be checked by taking medical history and performing a general physical examination. Finally, venous blood will be taken for the assessment of immunological parameters.

### Informed consent

The trial will be conducted in agreement with the principles of the Declaration of Helsinki (Edinburgh 2000). The investigator will explain the benefits and risks of participation in the study to each subject and will provide an informed consent form approved by the ethical review board of the University Medical Center Utrecht. The patient is then asked to sign the form prior to inclusion into the study. Data from this study will be treated confidentially and publication of the results of this study will be performed anonymously.

### Placebo run-in and adherence

A placebo run-in procedure will be set up to test the participant's adherence behavior in advance of the actual study. Patients meeting the inclusion criteria will be asked to take the add-on study medication (only placebo, no pantoprazole) during two weeks and will be asked to return the empty blisters to the researcher for administrative reasons. Only participants showing greater than 80% adherence (more than 80% of medication taken) will be randomized. During the trial the participants and their close relatives/friends will be informed about the importance of continuation of taking the study medication and returning the empty blisters to the researcher. Adherence will be checked by counting the returned empty blisters and determining plasma salicylic acid at months two and three. All participants will be kindly asked not to use any drugs such as marijuana or hashish within 24 hours before visit.

### Baseline assessments

As patients will be randomized in strata of relative TH-2 reactivity a blood sample will be taken at the beginning of the placebo run-in in order to have the immunological parameters determined by the time of randomization. At most one week before randomization, the severity of baseline psychotic symptoms will be assessed using the PANSS. In addition, a short cognitive test battery focusing on verbal learning and motor performance (e.g. California verbal learning test, Purdue Peg Board test, trail making test, HQ-Continues Performance test) will be administered.

### Randomized intervention

Patients will be randomized in a 1:1 ratio to either supplementation of acetylsalicylic acid or placebo in addition to their current antipsychotic treatment. Randomization will be performed in strata of psychiatric center (tertiary or non-tertiary) and relative TH-2 reactivity (high/low), delineated by the median IFN-γ/IL-4 ratio. To this end a computer-generated list will be produced with allocation codes in random order, balanced in the four strata by using permuted blocks. The aspirin dose is based on a trade-off between a dose that has a relatively low risk of gastro-intestinal toxicity in young persons, and the dose that is presumed to be anti-inflammatory, the latter being adopted from therapeutic doses used in the treatment of musculo-skeletal disorder[18]. Placebo will be identically packaged, looking and tasting tablets. For optimal gastro protection, all patients (also those randomized to placebo) will be given 40 milligrams of pantoprazole daily[19].

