### Study size

The planned number of patients to be included in this trial is 80, 40 in each arm. This is sufficient to show a statistically significant difference between the intervention arms of effect size (Cohen's *d*) ≥ 0.66 for the change in total PANSS score from baseline to last follow-up. It is based on an alpha of 0.05, a power (1-beta) of 0.8 and a two-sided unpaired t-test. Further, we accounted for 10% withdrawal. It should be noted that the power of the repeated measures analyses is considerably higher.

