### Data analysis

The statistical significance of the difference in the change in total PANSS score, its subscores, cognitive functions, immunological parameters from baseline to last follow-up between the arms and psychoactive medication will be tested using a two-sided unpaired t-test and its magnitude will be supplied with a 95% confidence interval. In addition, all outcomes will be analyzed as dependent variables in repeated measurements analyses with treatment arm as the independent variable. To study whether the potentially beneficial effect of acetylsalicylic acid is modified by initial relative TH-2 reactivity, we will repeat the analyses in strata of IFN-γ/IL-4 ratio The analyses will primarily be 'intention-to-treat'. In addition, a per protocol analysis will be performed on those who showed more than 90% adherence. If despite randomization important baseline differences in prognostic factors exist, adjustments will be made by including the corresponding variables as independents in the multivariable models. Finally, the change in psychopathological symptoms will be related to the change in immunological parameters using multivariable regression models. In these analyses adjustments for confounders will be made when appropriate.

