### Duration

We estimate that recruitment of patients will take 1 year. Follow-up will last 3 months. Assuming that data analysis and reporting require around 9 months, the total duration of the trial will be approximately 2 years.

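### The TH-2 stratification cut is a median of unstated origin, the analysis strata are not tied to it, and effect modification is not tested directly

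*Protocol article*

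**What the plan says.** All places are in the protocol article.

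- *Study objectives*: "A secondary objective is to examine whether this effect is modified by initial relative TH-2 reactivity". The same question stands under *Research questions*.
- *Baseline assessments*: blood is drawn at the start of the run-in "in order to have the immunological parameters determined by the time of randomization". Each patient's own ratio is therefore available when that patient is allocated.
- *Randomized intervention*: one stratification factor is centre type (tertiary or not). The other is "relative TH-2 reactivity (high/low), delineated by the median IFN-γ/IL-4 ratio". The list is "balanced in the four strata by using permuted blocks".
- *Duration*: "We estimate that recruitment of patients will take 1 year".
- *Data analysis*: the stated tests are an unpaired t-test and repeated-measurements models with treatment arm as the independent variable. Other variables enter only if important baseline differences appear. For effect modification, "we will repeat the analyses in strata of IFN-γ/IL-4 ratio".

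**The concern.** A patient's ratio can be called high or low only against a cut that already exists. The text names a median but not the sample it comes from, its value, or when it is set. The most natural candidate, the median of the trial's own patients, is complete only after the last baseline assay. *Immunological measurements* describes cytokines both in culture supernatants and in plasma, and the randomisation section does not say which of these gives the ratio.

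The analysis strata are named just as loosely. Nothing says that they are the randomised strata, so the boundary could be drawn again after outcomes are known. The balance that stratification was meant to give within each subgroup could then be partly lost.

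The stated analysis has two further weaknesses. It stratifies the randomisation but leaves the factors out of the models, which gives away precision. It also addresses modification only by repeating the analysis in each stratum, and two separate results do not test whether the effects differ.

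**Working it through.** **1. The plan's own figure.** *Study size* states: "The planned number of patients to be included in this trial is 80, 40 in each arm". The inputs are d = 0.66, two-sided alpha 0.05, power 0.80 and 10% withdrawal.

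- n per arm = 2 × ((1.960 + 0.8416)/0.66)² = 36.04.
- Allowing for withdrawal: 36.04/0.9 = 40.04 per arm, about 80 in all.
- Power with 36 per arm: 0.80 by the normal formula, 0.789 by the t-test.

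The figure reproduces to rounding, and nothing below changes it.

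**2. Mismatch if the two cuts differ.** Simulation: 80 patients in sequence, a continuous ratio, 10,000 runs. Imbalance was taken from 3,000 of these runs, with block size 4 and an even split of centre types. Block size and centre split are assumptions, since the article gives neither.

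| Cut at randomisation | Cut in analysis | Mean patients changing stratum, of 80 |
|---|---|---|
| Any cut | Strata as randomised | 0 |
| Running median | Final median | 5.1 (5th to 95th percentile 2 to 10) |
| Median of 10 earlier patients | Final median | 9.7 |
| Median of 100 earlier patients | Final median | 4.7 |

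In the running-median case, 5.1/80 is about 6%, and fewer than 1% of runs have no mismatch. The mean difference in arm size within the high stratum rises from 1.0 to 1.8 patients, and its 95th percentile from 2 to 4.

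**3. What that imbalance costs.** The information in a comparison with fraction p in one arm, relative to an even split, is 4p(1 − p). In a stratum of 40:

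- a difference of 1.8 is 20.9 against 19.1, so 4 × 0.5225 × 0.4775 = 0.998;
- a difference of 4 is 22 against 18, so 4 × 0.55 × 0.45 = 0.99.

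The loss of precision from this source is 1% or less.

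**4. What repeating the analysis in strata can show.** With 36 per arm completing and an even split, each stratum has 18 per arm.

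- Standard error of the effect in one stratum, in SD units: √(2/18) = 0.333.
- Power in one stratum if the true effect is 0.66: Φ(0.66/0.333 − 1.96) = Φ(0.02) = 0.51 (0.49 by the t-test).
- If the effect is 0.66 in both strata, so that there is no modification at all, the chance that exactly one stratum is significant is 2 × 0.51 × 0.49 = 0.50.
- Standard error of the difference between strata: √(2/18 + 2/18) = 0.471. The difference detectable with 80% power is 2.8016 × 0.471 = 1.32 SD, twice the 0.66 planned for the overall effect.

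A pattern of one significant and one non-significant stratum would therefore arise about half the time without any modification. Only a very large true difference between two strata could be shown.

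**The case against.** A reader might infer that the strata cannot be formed at all. The document does not support this. It holds only if the median means that of the trial's completed sample, and the text does not say so. A median from earlier samples or a running median fits the wording and would work.

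A reader might also infer that the analysed strata will differ from the randomised ones. That is stated nowhere. The article calls both of them strata of the same ratio, and a reading in which they are identical is natural. The mismatch is then zero.

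This is also a condensed article. A numerical cut-off, like a block size, is a detail that the full protocol may hold, and its absence alone is no defect. The harm shown is small. Larger losses can be produced only by assuming how far a cut-off might be off-centre, and the document gives no basis for such an assumption.

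These objections stand, and they limit the point to a modest risk in a secondary analysis. They do not reach the analysis that the article does state: models with treatment arm alone, plus adjustment that depends on observed imbalance, and modification judged by repeating the analysis in strata. An analysis plan that is not shown may refine this.

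**Conclusion.** The point holds in a limited form. The cut that defines high and low TH-2 reactivity is not tied to a stated sample, and the analysis strata are not tied to the randomised ones. The stated models do not carry the randomisation factors, and the within-strata analyses do not test modification directly.

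Randomisation and the primary comparison remain valid. The mismatch averages about 5 of 80 patients, provided that a running median is used for allocation and the final median for analysis. It is zero if the randomised strata are analysed. The more useful gain lies in the modification test: separate within-stratum tests would suggest a difference about half the time when the effect is 0.66 in both strata (assuming 72 completers, evenly split).

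**What to change.** - Before the first randomisation, set one IFN-γ/IL-4 cut-off, state its source and assay, and keep it throughout.
- Include the strata as randomised (TH-2 and centre type) as covariates in the models, whatever the baseline differences turn out to be. Use the TH-2 stratum as randomised as the subgroup definition.
- Test effect modification with a treatment-by-log(IFN-γ/IL-4) interaction, the ratio being continuous. Report the within-stratum estimates with confidence intervals as description.

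The cost is one number and a few sentences, and the sample size does not change. There are two downsides. A fixed cut-off may not split the sample evenly, especially if it comes from few samples. In the same simulation, a median from 20 earlier patients puts 24 to 55 of 80 in the high stratum (5th to 95th percentile). By 4p(1 − p), a two-stratum comparison at those limits keeps 4 × 0.30 × 0.70 = 0.84 and 4 × 0.6875 × 0.3125 = 0.86 of the information. With 100 earlier patients the range is 30 to 50, and 0.94 is kept. The continuous test does not depend on the cut, but it assumes a roughly linear relation on the log scale, which should be checked.

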### Concomitant medication

As an analgesic the patients will be emphatically advised to take acetaminophen instead of acetylsalicylic acid or other NSAIDS. A record of all medication taken will be kept during the entire trial.

### Adverse reactions

Acetylsalicylic acid use may cause dyspeptic complaints, ulcer disease and gastrointestinal bleeding. However, due to its strong association with high age (odds ratio 1.04 per year[20]), we expect that the risk of ulcer or serious bleeding is considerably lower than 1% per year that was observed in persons over 60 years of age taking similar doses of aspirin[21]. Further, all patients will be given 40 milligrams pantoprazole daily which has shown to reduce the risk of NSAID induced gastrointestinal problems considerably[19]. Nevertheless, at every follow-up visit the participants will be asked about epistaxis, hematemesis, melena, rectal bleeding and hematuria. Further, dyspeptic complaints will be systematically recorded at every visit using an 8-item self-administered questionnaire [22]. Patients will be urged to stop taking study medication one week in advance of molar extractions or similar surgical procedures and to continue not before one week after the procedure. In case of medical emergencies the initial care will be managed by the general practitioner as in usual care, if possible after consultation of the investigator, or the person taking medical responsibility for the participants in this study (Prof. dr [name]). At a later stage the investigator will consult the treating psychiatrist and the patient's general practitioner whether continuation in the trial is reliable.

### Study outcomes

The primary outcome of this trial is the 3-month change in positive and negative symptoms on the total PANSS score. Secondary outcomes are the 3-month change in the PANSS subscales, cognitive symptoms, immunological parameters (γ-interferon, IL-4, IL-6 and IL-12), and psychoactive medication taken during the trial.

### Follow-up assessments

At one, two, and three months, and in case of withdrawal from the study, the severity of positive and negative symptoms will be reassessed using the PANSS. The cognitive tests will be repeated at three months or at study discontinuation. Blood samples will be taken at 2 and 3 months, or at withdrawal, for determination of the Aspirin levels. All assessments will be performed blind to medication status. The overview of the visits can be seen in table 1.

**Table 1 T1:** Overview of assessments/interventions

	Start of run-in	Baseline	1 Month	2 Months	3 Months (@)
Informed Consent	X	-	-	-	-
Screening	X	-	-	-	-
Pregnancy test	X	-	-	-	-
Randomization	-	X	-	-	-
Immunological parameters	X	-	-	X	X
Blood for DNA isolation	X	-	-	-	-
Aspirin concentration	-	-	-	X	X
PANSS	-	X	X	X	X
CASH (+)	X	-	-	-	-
Cognitive tests	-	X	-	-	X
Adverse events	-	-	X	X	X
Co-medication	X	X	X	X	X
Compliance	-	X	X	X	X

@ or withdrawal

+ if previous CASH is longer than 6 months ago

